## Abstract

**Introduction:**

Approximately 17% of adults with intellectual disabilities (ID) living in the community display behaviours that challenge. Intensive support teams (ISTs) have been recommended to provide high-quality responsive care aimed at avoiding unnecessary admissions and reducing lengthy inpatient stays in England. We have identified two models of ISTs (model 1: enhanced provision and model 2: independent provision). This study aims to investigate the clinical and cost-effectiveness of the two models of ISTs.

**Methods and analysis:**

A cohort of 226 adults with ID displaying behaviour that challenges who receive support from ISTs from each model will be recruited and assessed at baseline and 9 months later to compare the clinical and cost-effectiveness between models. The primary outcome is reduction in challenging behaviour measured by the Aberrant Behaviour Checklist-Community (ABC-C). The mean difference in change in ABC score between the two IST models will be estimated from a multilevel linear regression model. Secondary outcomes include mental health status, clinical risk, quality of life, health-related quality of life, level of functioning and service use. We will undertake a cost-effectiveness analysis taking both a health and social care and wider societal perspective. Semistructured interviews will be conducted with multiple stakeholders (ie, service users, paid/family carers, IST managers/staff) to investigate the experience of IST care as well as an online survey of referrers to capture their contact with the teams.

**Ethics and dissemination:**

The study was approved by the London–Bromley Research Ethics Committee (REC reference: 18/LO/0890). Informed consent will be obtained from the person with ID, or a family/nominated consultee for those lacking capacity and from his/her caregivers. The findings of the study will be disseminated to academic audiences, professionals, experts by experience and arm’s-length bodies and policymakers via publications, seminars and digital platforms.

**Trial registration number:**

ClinicalTrials.gov Registry (NCT03586375).

Strengths and limitations of this studyThis study will be the first systematic national evaluation of intensive support team (IST) models for adults with intellectual disability who display challenging behaviour.Accessing the experience of stakeholders (eg, IST managers, staff members, family and paid carers, and service users) will enable an in-depth understanding of how ISTs function and how they respond to people with complex needs.This is not a randomised controlled trial so may be subject to biases associated with observational research.

## Introduction

People with intellectual (also called learning) disabilities (ID), characterised by cognitive delay and difficulties in adaptive functioning, constitute approximately 1% of the population.^1^ Seventeen per cent of adults with ID, living in the community, present with serious challenging behaviour including aggression, self-injury or other socially inappropriate behaviours.^2^ As many as 100, 000 children and adults are estimated to be at risk of admission to inpatient care due to the presence of such behaviours if they are not effectively supported in the community.^3^ There are ongoing concerns that these individuals are subject to increased rates of hospitalisation, unnecessary long-term use of psychotropic medication, poorer health, abuse and exclusion.^4^

Intensive support teams (ISTs) are specialist teams which have been advocated for many years as the best services to help people with ID and challenging behaviour remain within their local communities. The teams may be staffed by one or more professions (eg, psychology, nursing, psychiatry). They deliver interventions such as positive behaviour support, support adults with ID who are in a mental or behavioural crisis, and provide inreach when a person is admitted to a psychiatric inpatient facility.^5 6^ ISTs are recommended to provide high-quality proactive and responsive care aimed at avoiding unnecessary admissions or reducing inpatient length of stay and maintaining people in their local community.^6 7^ However, there is little evidence to recommend a preferred IST model or way of implementing these aims, and there has not been a comprehensive attempt to describe the clinical and cost-effectiveness of ISTs. Such information would be needed by health funders in order to fund services fit for purpose. The National Institute of Health and Care Excellence Guideline (NG11)^8^ reports that: ‘It is widely recognised that locally accessible care settings could be beneficial and could reduce costs but there is no strong empirical evidence to support this’.

Previous studies describe either demonstration projects following the closure of institutions^9 10^ or region-wide implementation of standalone services.^11^ Three small controlled trials have examined, respectively: (1) a standalone specialist-support service delivering standard treatment in addition to behaviour therapy in one area in England^12^; (2) a standalone team delivering assertive outreach for adults with ID who display challenging behaviour in inner London^13^ and (3) an active case management model.^14^ Comparator treatment was usual care in all three studies. The remit of the ISTs differed between studies, with one providing support to people who display challenging behaviour while the other two provided a replication of the intensive support management from adult mental healthcare. These small studies presented equivocal findings in terms of reduction in challenging behaviour, improved level of functioning and quality of life dependent on the model.

A study^15^ showed that positive behavioural outcomes may be achieved by an embedded IST model in which a core team of community ID service staff trained in managing challenging behaviour meet together regularly to discuss referrals with specialist supervision and peer support by the lead clinician. Literature from other population groups (eg, dementia care)^16^ and adult mental health^17^ suggests that home treatment teams may be effective in managing crises and reducing admissions. Wheeler *et al*^18^ showed that stakeholders in adult mental healthcare have a number of expectations from crisis resolution teams and this is likely to be the case for ISTs in the field of ID. So far, there has been limited reporting on stakeholder experiences of ISTs,^15 18^ so little is known whether service users and paid and family carers find the involvement of IST staff and frequency of contact helpful and acceptable.

As part of the Transforming Care programme,^19^ the National Health Service (NHS) England has prioritised ISTs as a central pillar in the arsenal of support for individuals who display challenging behaviour, and has invested in a variety of formats of such teams in areas with high admission rates. The current study is the second phase of a wider project that set out to systematically examine the implementation of ISTs in England.

The first phase identified two IST service models^20^: enhanced provision (model 1) and independent provision (model 2) following an England-wide survey of ISTs (n=73).^20^ The components of each model as reported by professionals in the survey are shown below (table 1).

**Table 1 T1:** Characteristics of IST models

ISTs	
Model 1—enhanced provision	Model 2—independent provision
Integrated within the broader Community Intellectual Disability Services	Separate from Community Intellectual Disability Services
Long-term support (more than 6 months)	Short-term support (3–12 months)
Accept self-referrals	Referral via professionals
Large caseload (20+)	Small caseload (up to 15)
Less likely to use outcome measures	Use of outcome measures

IST, intensive support team.

There is limited evidence for the comparative clinical and cost-effectiveness of either enhanced or independent provision^15^ and of long-term clinical gains. Furthermore, satisfaction of stakeholders with the ISTs has hardly featured in the literature and that deserves better understanding if the ISTs are fit for purpose and responsive to patient need.

## Objectives

The overall aim of phase 2 of the study is to investigate patient outcomes (eg, challenging behaviour, risk, adaptive behaviour, service use, quality of life) and service-level outcomes (eg, engagement with the IST, satisfaction with referral process, number of referrals, experience of care provided).

### Specific objectives

To generate evidence regarding which IST model best supports improved outcomes for adults who display challenging behaviour.To estimate the costs of the two IST models and examine cost-effectiveness.To explore views and experiences of ISTs among relevant stakeholders (service users, paid and family carers, and service providers).To investigate how ISTs impact the lives of adults with IDs who display challenging behaviour in their caseload, their families and the local services.

Findings will generate evidence to inform and support decision-making on commissioning of ISTs for adults with ID who display challenging behaviour.

## Methods and analysis

The research team will compare the two models, enhanced provision and independent provision, respectively, of ISTs already identified in phase 1 of the study.^20^ The research assistant or clinical study officers will collect study participant-level outcomes at two assessment points (baseline and 9 months) and service-level outcomes over the same time period. The research assistant will also collect qualitative data to understand the experiences and views of key stakeholders, and stakeholder experiences of the different models.

### Setting and participants

Eight enhanced service provision ISTs and eight independent service provision ISTs (table 1) will be selected at random from ISTs surveyed in phase 1 of the study.^20^ Service users, either already under the care of the 16 ISTs or newly referred, and their caregivers will be identified by IST staff either at first clinical assessment or from the IST services caseloads and asked if they are interested in taking part in the study. Following an expression of interest, the researchers will contact them to provide information about the study and to obtain written or audio-recorded informed consent from those agreeing to undergo further research assessments.

### Inclusion criteria

Service: IST adheres to one of the identified models (table 1); has been operational for at least 12 months; there is commitment to fund it for the study duration and it can achieve the sample size estimates.Service users: receive support from IST service; mild to profound ID based on clinical diagnosis; aged 18 years and over.

### Exclusion criteria

Service: has been operational for less than 12 months at selection or there are plans to dissolve it.Service users: primary clinical diagnosis of personality disorder or substance misuse; decision by clinical team a referral to the study would be inappropriate (eg, due to ongoing legal challenges to the service or the person being acutely unwell).

### Consent

Consent will be sought from service users and their respective carers (ie, paid and family) and/or nominated consultees where the participant with ID lacks capacity in accordance with the Mental Capacity Act 2005.^8^ For those service users with decision-making capacity, the researcher will speak to the potential participant by phone or in person and will give or send the service user participant information sheet (in Easy Read format) to inform them of the study. If the service user agrees to take part in the study, the individual will complete a written consent form or consent will be taken by telephone and audio-recorded for purposes of verifying consent. The researcher will then repeat the above process (using the carer participant information sheet) with the service users’ paid or family carer to seek their consent to take part and complete the rest of the study measures. For those service users lacking decision-making capacity, the researcher will approach the personal or nominated consultee for that person (using the consultee information sheet) and seek written or audio-recorded advice about including the service user in the study.

### Outcome measures

#### Study participant-level outcomes

Each participant will be recruited at any point of IST care and will be assessed at baseline and at 9 months which reflects the time period an IST may be expected to be involved in working with a participant. This length of follow-up was chosen because our research and clinical experience indicates that, while there is a range of duration for IST involvement, assessment and delivery of behaviour support plans usually require about 3 months to complete and adults with ID and challenging behaviour often remain in the care of the IST for approximately 12 months.

The primary outcome is challenging behaviour measured by the Aberrant Behaviour Checklist-Community (ABC-C)^21^ which has been widely used in the target population and is completed by the caregiver (eg, family, paid care home staff, IST staff).

A range of secondary endpoints examine the following: the carer-reported Psychopathology Assessment for Adults with Developmental Disabilities checklist 22 is a mental health screening tool which provides sufficient information on potential mental health comorbidity that is often underascertained in adults with ID. The Threshold Assessment Grid^23^ measures clinical risk in adults with ID. The Quality of Life (QoL)^24^ will be used with the individual with ID and/or the caregiver, if participants lack capacity, to measure the individual’s quality of life. The Adaptive Behaviour Scale-Short Form assesses level of functioning.^25^ The Client Service Receipt Inventory (CSRI)^26^ (adapted for the study, 6-month retrospective service use at each assessment point) is a widely used service-use questionnaire and has been validated for use in mental health and ID services research.

Health-related quality of life will be measured by the EQ-5D-5L.^27^ The EQ-5D is used to generate quality-adjusted life years (QALYs). The self-report version will be used with the individual with ID where possible, and the proxy version will be used with the caregiver in the cases of participants lacking capacity.

The researchers will collect sociodemographic information, as well as number of hospital admissions and maintenance of accommodation at follow-up.

The study participant flow chart is shown in figure 1.

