#### Statistical analysis plan

As per the predetermined statistical analysis plan, the baseline characteristics of participants will be summarised separately for the two IST models. Categorical variables will be reported as counts and percentages, while continuous variables will be summarised as means and SDs or medians and IQRs as appropriate depending on the distribution of the data.

The primary outcome is challenging behaviour measured by total score on the ABC. Change in ABC total score from baseline to 9-month follow-up will be calculated for each participant. The mean difference in ABC score between the two IST models will be estimated from a multilevel linear regression model with change in ABC score as the outcome, a fixed effect of model as the main exposure, and a random effect of IST to account for clustering within services.

Age, gender, living arrangements, level of ID, level of risk, presence of autism and clinical comorbidities have been identified as potential confounders and will be specified as covariates in adjusted multilevel linear regression models similar to the main unadjusted model described above. The estimated difference in change in ABC total score from both unadjusted and adjusted models will be reported with accompanying 95% CI and p value.

The secondary outcomes detailed above will be analysed using statistical models analogous to those for the primary outcome. Binary outcomes will be analysed using multilevel logistic regression models. Non-normally distributed continuous outcomes will be analysed using the bootstrap method and bias corrected 95% CI will be reported. P values will not be reported for secondary outcomes.

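### Time already in IST care at baseline is in neither analysis model, although entry is open at any point of care and the two models differ in length of support

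*Protocol article*

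**What the plan says.** Under Study participant-level outcomes, the protocol article says: "Each participant will be recruited at any point of IST care and will be assessed at baseline and at 9 months". Setting and participants confirms that recruits may be "either already under the care of the 16 ISTs or newly referred". Neither section states a quota, a stratification or a limit on time since referral.

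Table 1 in the Introduction gives the enhanced model as "Long-term support (more than 6 months" and the independent model as "Short-term support (3–12 months", in each case with the bracket closing after the figure. The Inclusion criteria make this table the basis for classifying a service: "IST adheres to one of the identified models (table 1".

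The Statistical analysis plan section takes change in ABC total score from baseline to 9 months as the outcome. The main model is unadjusted, with a fixed effect of IST model and a random effect of IST. For the adjusted models, "Age, gender, living arrangements, level of ID, level of risk, presence of autism and clinical comorbidities have been identified as potential confounders". Neither months in care nor new-versus-existing status is on that list, and nor is baseline ABC score.

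On timing, the article says that "assessment and delivery of behaviour support plans usually require about 3 months to complete" and that people often stay with an IST for roughly a year.

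**The concern.** Baseline here is the date of the study assessment, not the start of IST care. By the article's own timing, it may fall before, during or after delivery of the behaviour support plan. If improvement comes mainly in the early months, the change still to be seen over the next 9 months depends on how far into care the person already is.

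That would add only noise if both groups were sampled at similar stages. The models are, however, partly characterised by how long they keep people. A draw from existing caseloads can therefore be expected to find people further into care where support lasts longer. The share of new referrals may also differ by model, and nothing in the article controls it. Two equally effective models could then show different 9-month change, and a larger sample would not remove the difference. The first specific objective is to find which model best supports improved outcomes, so this affects the main comparison.

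**Working it through.** **The plan's own figure.** Inputs from Sample size: 0.45 SD, 5% significance (taken as two-sided), 80% power, intraclass correlation 0.02, 15% loss. Setting and participants gives 8 ISTs per model.
- Without clustering: 2 × ((1.96 + 0.84)/0.45)² = 77.5, so 78 per model.
- Design effect with 96/8 = 12 analysed per IST: 1 + 11 × 0.02 = 1.22. Then 78 × 1.22 = 95.2, so 96 per model.
- Loss to follow-up: 96/0.85 = 112.9, so 113 per model and 226 in total.

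The stated sample size reproduces, and this point does not affect it. The implied standard error of the difference is √(2 × 1.22/96) = 0.159 SD.

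**Simple illustration.** Nothing in the documents gives the distribution of time in care, so everything from here on is assumption. Let the total benefit be 1 SD, accruing as 1 − exp(−t/τ). A person s months into care at baseline then gains exp(−s/τ) − exp(−(s+9)/τ) over 9 months. For s uniform on (0, L) the mean is (τ/L)(1 − exp(−L/τ))(1 − exp(−9/τ)).

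| τ (months) | New referral | L = 12 | L = 24 | L = 12 minus L = 24 |
|---|---|---|---|---|
| 3 | 0.95 | 0.233 | 0.119 | 0.11 (25% of 0.45) |
| 6 | 0.78 | 0.336 | 0.191 | 0.15 (32% of 0.45) |

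These figures scale with the assumed benefit: at a total of 0.45 SD the last column becomes 0.05 to 0.07 SD. It also halves, to 0.06 to 0.07 SD, if half of each group is newly referred.

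**Illustration closer to Table 1.** Length of care is uniform on 3-12 months in the independent model, and on 6 to 12, 18, 24 or 36 months in the enhanced model. Existing clients are sampled at a random point of care. Both models follow the same curve (τ = 3 or 6, total 1 SD), and gain stops when care ends. A positive difference disfavours the enhanced model.

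| Newly referred, enhanced / independent | Mean months in care at baseline, enhanced / independent | Spurious difference (SD) |
|---|---|---|
| 0% / 0% | 4.7-12.3 / 4.2 | −0.01 to +0.14 |
| 25% / 25% | 3.5-9.2 / 3.2 | −0.03 to +0.09 |
| 50% / 50% | 2.3-6.1 / 2.1 | −0.04 to +0.03 |
| 20% / 50% | 3.7-9.8 / 2.1 | +0.09 to +0.28 |

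The last row depends on which model has more new referrals; swapping the two shares reverses the sign. Because gain stops at discharge, these figures combine phase at entry with the care still to come. If gain instead continues along the curve after discharge, half new in both models gives 0.01 to 0.02 SD for enhanced care of 6-12 months and about 0.075 SD for 6-24 months.

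**Consequence for inference.** At a standard error of 0.159 SD, a bias of 0.10 SD raises the type I error from 5% to 9.6%, and a bias of 0.20 SD raises it to 24%. A bias of 0.10 SD against a true 0.45 SD effect lowers power from 81% to 59%.

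**The case against.** The strongest reply is that neither the direction nor the size of any bias can be read from the documents. One entry rule applies to every IST. The Table 1 characteristics were reported by professionals in a survey, and the ranges share 6 to 12 months. The 1 SD benefit, the 24-month caseload and the accrual curve are all supplied from outside, while the Introduction calls earlier findings equivocal. Many independent-model participants would leave care before the 9-month visit, so any loss of benefit after discharge could act in the opposite direction. All of this stands. It limits the claim to possible confounding of unknown sign and size.

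The remedy also has limits. The main model is unadjusted, so a new covariate leaves that estimate as it is. Time in care at baseline is itself partly a product of the model's length of support. Adjustment does not correct for selecting those still on the caseload. The small and static caseloads reported under Study progress suggest that an early-entry subset may be thin. These points also stand, and they shape the fix.

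The reply that such detail belongs to the unseen analysis plan does not carry. The article itself states both the entry rule and the confounder list, so the omission is from a stated list. Its acknowledgement of observational bias is only general.

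A reader might infer that new referrals in one model are set against existing clients in the other, giving 0.78 − 0.34 = 0.44 to 0.95 − 0.23 = 0.72 SD, about the whole target or more. The documents do not support this: new and existing clients are eligible under both models. Nor does larger caseload size by itself show longer prior exposure.

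**Conclusion.** The point holds as a gap in the stated adjustment. Entry is open at any stage of care, the models are characterised by different though overlapping lengths of support, and time already in care is in neither the unadjusted nor the adjusted model. Nine-month change may therefore reflect different phases of care in the two groups.

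With equally effective models the illustrations run from about zero (slightly negative in some cases) to 0.1-0.3 SD, against the 0.45 SD target. The upper end needs unequal shares of new referrals. All of these figures rest on the assumed total benefit, accrual curve, caseload lengths and shares. The bias would probably disfavour the longer-stay model. A reader might conclude that it certainly does, or that the two groups are at different stages by definition; the documents establish neither.

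**What to change.** Recruitment has closed, so the entry rule stands and the change is to the analysis.

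- Take each participant's IST referral or first-assessment date from IST records. The study already collects time to first assessment at service level.
- Add time in care at baseline to the stated confounders in the adjusted model, as new versus existing plus a linear or flexible term in months.
- Say in advance that the model comparison will be interpreted from this adjusted estimate alongside the unadjusted one.
- Specify, before the comparative analysis, a sensitivity analysis in newly referred or early-entry participants, for example those within about 3 months of IST entry.
- Do not adjust for total length of care, which is part of what distinguishes the models.

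The cost is one extra date per participant and one or two model terms. Some precision will be lost because time in care is correlated with model, and the early-entry subset may be too small for more than a rough check. Selection of people still on the caseload remains a limitation to report.

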#### Qualitative substudy: stakeholder’s views of ISTs

An embedded qualitative substudy will allow to investigate how IST care is experienced by service users and family carers, and to obtain a multiperspective view of IST functioning within local service contexts, based on user, carer and practitioner views. The researchers will conduct semistructured interviews with (1) IST managers and staff, (2) service users, and (3) family and paid carers. Up to eight service users per IST model, including those who may need support to communicate (provided by family or paid carers); and up to eight carers (a mixture of family and paid) per IST model will be included. The researchers will also attempt to interview a small number of family carers who have recently declined IST contact. Purposive sampling will be employed, in order to include a range of ages, work experience, professional backgrounds, and carer roles and relationships in our sample. In order to gain a broad perspective on IST implementation in England, the researchers will aim to conduct interviews with all managers of the IST services taking part in the phase 2. Interviews with IST managers and staff will be conducted in the early stages of the research study; interviews with service users and family and paid carers will be conducted near the time of discharge from IST services or around the 9-month follow-up, whichever is sooner.

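### IST staff may complete the ABC-C primary outcome although their own service is being compared, and this is not reconciled with the consent section, where a paid or family carer completes the measures

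*Protocol article*

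**What the plan says.** Protocol article, Study participant-level outcomes: the ABC-C "is completed by the caregiver (eg, family, paid care home staff, IST staff" being the examples given. IST staff are thus named as acceptable raters of the primary outcome.

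Protocol article, Consent: "Consent will be sought from service users and their respective carers (ie, paid and family" is how carers are defined, and the researcher then approaches the "paid or family carer to seek their consent to take part and complete the rest of the study measures". IST staff do not appear there.

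Protocol article, Qualitative substudy: interviews are planned with three groups, "1) IST managers and staff, (2) service users, and (3) family and paid carers". IST staff are kept apart from paid carers, so the term paid carer does not readily cover them.

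Protocol article, Statistical analysis plan: the outcome is change in ABC total score, modelled with "a fixed effect of model as the main exposure, and a random effect of IST to account for clustering within services".

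Protocol article, Methods and analysis: "The research assistant or clinical study officers will collect study participant-level outcomes at two assessment points (baseline and 9 months". Research staff gather the form, but the rating on it is the informant's.

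**The concern.** The ABC-C is an informant rating. Where the informant belongs to the IST, the service under comparison judges its own result. The article does not mention blinding, but a team necessarily knows which service it works in.

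The primary endpoint is at stake, and with it part of the economic evaluation, where ABC is one of the effects valued in the net benefit calculation. Because change from baseline is analysed, a move from one kind of rater to another between visits is counted as a change in behaviour.

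The two sections also give a site different instructions. A researcher following the Consent section would look for a paid or family carer. One following the outcome section could accept a member of the team.

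**Working it through.** **1. The passages side by side.**
- Outcome section: family, paid care home staff and IST staff may rate.
- Consent section: carers are paid and family, and one of them completes the measures.
- Qualitative substudy: IST staff form a group separate from paid carers.

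The first statement is wider than the second, and the third closes off the reading that would join them. The consent sentence comes in the text on service users with capacity, and the outcome list is introduced as examples. This is therefore an inconsistency to reconcile and not a breach of a stated ban.

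**2. The plan's own sample size, for scale.** Inputs from Sample size: 0.45 SD, 5% (taken as two-sided), 80% power, ICC 0.02, 15% loss. Setting and participants gives 8 ISTs per model.
- Per model without clustering: 2 × (1.960 + 0.842)² / 0.45² = 77.5 (78.5 from the t distribution).
- Design effect with 96/8 = 12 per IST: 1 + 11 × 0.02 = 1.22.
- 78.5 × 1.22 = 95.8, so 96. Then 96/0.85 = 112.9, so 113.

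The stated 96 and 113 are reproduced, and nothing in this point changes them. The standard error of the contrast is √(2 × 1.22/96) = 0.159 SD, taking the SD unit to be that of the analysed outcome.

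**3. When IST rating biases the contrast.** Take carer ratings as the reference. In model m let pB and pF be the shares rated by IST staff at baseline and follow-up, and bB and bF the mean bias of those ratings in SD.
- Shift in mean change in model m = pF × bF − pB × bB.
- Bias in the contrast = shift in model 1 − shift in model 2.

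It follows that:
- Same informants at both visits and constant leniency: the shift is zero in each model, even if the shares differ between models.
- Equal shift in both models: the contrast is unbiased.
- Bias remains if the leniency drifts over time and either the drift or the share differs between models, or if the share changes between visits by a different amount in each model.

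**4. Illustration. Every p, b, d and c below is assumed; the article gives none of them.**

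(a) The same share p is IST-rated in both models at both visits, and the drift in rater bias differs by b between models. Bias = p × b.

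| p | b (SD) | Bias (SD) | Share of 0.45 | Type I error at nominal 5% |
|---|---|---|---|---|
| 10% | 0.2 | 0.02 | 4% | 5.2% |
| 25% | 0.5 | 0.125 | 28% | 12% |
| 50% | 0.5 | 0.25 | 56% | 35% |

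(b) IST ratings carry a constant bias c, but the net move into or out of IST rating between visits differs by d between models. Bias = d × c.
- 20 points × 0.3 SD = 0.06 SD, 13% of 0.45.
- 40 points × 0.5 SD = 0.20 SD, 44% of 0.45.

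The table and list show how the bias scales. They do not estimate it.

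**The case against.** The strongest reply is that most of the bias may cancel. A rater who is lenient at both visits drops out of a change score, and both arms are ISTs, so equal self-rating drops out of the contrast. This stands, and it limits the point to the conditions in step 3. IST staff may also serve only as a fallback where no other carer exists; the article does not say.

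Four stronger readings are tempting, and the documents do not support them.
- *The consent section forbids IST raters.* It describes whom the researcher approaches and states no exclusion.
- *Table 1 shows that IST rating differs by model.* For the enhanced model it says "Less likely to use outcome measures", and it lists use of outcome measures for the independent model. That is the services' own practice. It says nothing about who is the study informant, since research staff collect the study outcomes.
- *The plan fails to keep the same informant.* The article is silent, but such a rule commonly sits in the full protocol. Likewise, recording or adjusting for rater type may be in the analysis plan, which is not shown. These belong in the remedy and are not defects found.
- *Switching informants wrecks the power.* With a baseline to follow-up correlation r, the SD of change is √(2(1 − r)): 0.775 at r = 0.7 and 1.0 at r = 0.5, with power 95.4% and 80.6% at 96 per model. Both correlations are assumed, the plan never claims r = 0.7, and even the worse case meets the planned 80%.

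The article also concedes that "This is not a randomised controlled trial so may be subject to biases associated with observational research". That general caveat does not cover a rater drawn from the service under comparison, which the plan chose and can avoid where another carer exists.

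**Conclusion.** The article does allow members of the compared service to rate the primary outcome, and it does not reconcile this with its consent section. That much rests on the text. That such raters know their service model is an inference, but a safe one.

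Whether the model contrast is biased is not known. It needs IST rating to differ between models in frequency or in the drift of its bias, or informants to change between visits in a pattern that differs by model. A change pattern alike in both models would mainly add noise. The share of IST-rated participants is not given, so the size cannot be stated; under the assumed inputs it runs from negligible (0.02 SD) to more than half the target difference (0.25 SD). A reader might infer that the comparison is biased in favour of one model. Nothing in the document supports a direction.

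This is a cheap improvement: it protects the primary comparison and alters neither the main model nor the sample size.

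**What to change.** 1. Reconcile the Consent and Study participant-level outcomes sections. For any remaining assessments, a paid or family carer outside the IST rates the ABC-C wherever one is available, preferably the same person at both visits. This can reach few participants: enrolment closed in May 2020 and 180 follow-ups are complete. If enrolment reached the planned 226, which the article does not confirm, 226 − 180 − 13 lost = 33 remained.
2. Record informant type at both visits, or retrieve it for ratings already taken, and report it by IST model.
3. Prespecify two sensitivity analyses of the primary outcome: one excluding participants with an IST-staff rating at either visit, and one excluding those whose informant changed.
4. Do not adjust the main model for informant switching. It arises after baseline and may itself result from the service model, for example through discharge or a move, so adjustment could add bias.

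Cost: one variable at each visit, some retrieval work and two extra analyses. The sensitivity samples will be smaller and possibly selected, since people with no other carer may differ from the rest. As a guide to precision, excluding an assumed 25% leaves 72 per model, or 9 per IST. The design effect becomes 1 + 8 × 0.02 = 1.16 and the standard error √(2 × 1.16/72) = 0.180 SD, against 0.159. The results should be read for agreement with the main estimate and not for significance.
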